### Statistical analysis

All the efficacy analyses will be based on the intent to treat population, consisting of all randomized patients.

Incidence rates (aspirin vs. no aspirin) will be estimated using Kaplan-Meier survival curves that will be compared using logrank analysis. Additionally, treatment efficacy will be assessed by multivariate analyses using Cox's regression model.

Other secondary analyses will include the evaluation of efficacy of aspirin on all secondary end-points. Aspirin efficacy will also be tested in the following different circumstances:

- Men vs. women;

- Age ≥65 vs. <65 years;

- Type of diabetes;

- Metabolic control (quartiles of HbA_1c_);

- Baseline cholesterol levels (quartiles of total and LDL-cholesterol levels);

- Presence of microvascular complications (retinopathy, nephropathy);

- Treatment with other cardiovascular drugs (in particular β-blockers, ACE-inhibitors, Angiotensin Receptor Blockers).

The Mantel-Haenszel procedure will be applied to test for the linearity of effects across subgroups, while the chi-square test will be applied to test for heterogeneity of effects among the subgroups.

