### Study treatments

All randomized patients will be instructed to take one or two tablets daily; in particular, if the patient will be assigned to "aspirin+simvastatin arm", he will be instructed to take one tablet containing simvastatin (one 20 mg tablet every evening), and the other containing aspirin. Otherwise, the patient will be instructed to take one tablet containing simvastatin.

Study drugs will be prescribed by the investigator.

An initial dose of 20 mg/daily of simvastatin will be prescribed to patients not previously on treatment with statins.

The dose of simvastatin can be increased to 40 mg/day at month 3 in those patients whose plasma LDL cholesterol remains ≥100 mg/dL (2.59 mmol/L).

Patients already on statins treatment at study entry will be shifted to the equivalent dose of simvastatin without the need for a drug-free period.

Changes in simvastatin doses are allowed throughout the study based on clinical judgment.

If target LDL cholesterol levels will not be reached with 40 mg/daily, clinicians may modify therapeutic strategies (changes of statin, addition of other drugs such as ezetimibe, fenofibrate, nicotinic acid, omega-3 fatty acid).

Treatment will be centrally assigned on telephone, after verification of the correctness of inclusion and exclusion criteria. A separate computer-generated randomization table will be produced for each physician/diabetes centre in random permuted blocks. Each randomized patient will receive a unique subject identification number.

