### Sample size estimates

The sample size calculation is based on the cardiovascular event rate occurred in over 1000 diabetic patients without evidence of cardiovascular disease enrolled in the PPP trial [10]. This study was conducted with the participation of both General Practitioners and Diabetes Clinics in Italy, thus closely reflecting the setting of care and the context in which the ACCEPT-D trial will be conducted. In the PPP trial the cumulative incidence of major cardiovascular events (cardiovascular death, myocardial infarction, stroke, transient ischemic attack, peripheral vascular disease, revascularization procedures), after a median follow-up of 4 years, was of 11.5% in subjects not assigned to aspirin treatment (incidence rate of 2.88% per annum). Assuming that treatment with statins can reduce such an event rate by approximately one quarter (based on the results of the meta-analysis of primary prevention studies in patients with diabetes [26]), we can expect an incidence rate of major cardiovascular events of about 2.1–2.2% per annum. Since the primary cumulative end-point of the study also includes hospitalizations for major vascular causes, sample size calculations for the proposed trial are based on a conservative estimated 2.5% annual rate of major vascular events.

Aspirin has been shown to reduce major cardiovascular events by about one quarter in a wide range of high risk populations [27,28]. The sample size is thus estimated to detect with a statistical power of 90% (α = 0.05) a reduction in the risk of major cardiovascular events of 25% (HR = 0.75).

Given these assumptions, a total of 515 first events are needed for the primary efficacy analysis. Therefore, the total number of subjects to be enrolled is of 4.700 patients, to be followed up for five years. From the PPP trial [29], it is possible to foresee a trial discontinuation rate of 10%. Therefore, a total of 5.170 patients will be enrolled (2.585 in each treatment arm). A total of 515 events will also ensure an adequate statistical power (i.e. 80%) to detect a smaller reduction in the risk of major events (i.e. HR = 0.78).

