#### Data collection

For each randomized patient a minimum set of information will be collected at study entry. This will include clinical data regarding diabetes, cardiovascular risk factors, and selected concomitant medications. Information on laboratory parameters will also be collected, including HbA_1c_, lipid profile, serum creatinine, albumin-creatinine ratio, and liver enzymes. Investigators will be requested to report the value of the last measurement performed. If the last HbA_1c _measurement was performed more than 3 months before randomization and all the other measurements were performed more than 6 months before randomization, the measurement should be performed again, according to the standards of medical care for patients at high cardiovascular risk. Laboratory data will be abstracted from clinical records by the participating physicians and reported in ad hoc forms together with their reference ranges.

The same set of information will be collected at 6-month intervals, with the exception of albumin-creatinine ratio that will be collected annually (Table 1).

**Table 1 T1:** Overview of the visits and measurements

	Follow-up			
Visit Number	1	2	3–4–5...	Final visit
Month	0	3	6-month intervals	
Inclusion/Exclusion criteria	x			
Informed Consent	x			
Medical history	x			
Concomitant Medication	x	x	x	x
Weight	x		x	x
Height	x			
Waist circumference	x		x	x
Blood pressure/Heart rate	x		x	x
HbA_1c_	x		x	x
AST, ALT	x		x	x
Creatinine	x		x	x
Microlbuminuria	x		x	x
Albumin/creatinine ratio	x		x	x
Total cholesterol, HDL cholesterol, Triglycerides	x	x	x	x
Adverse events		x	x	x
Compliance		x	x	x
End-point verification		x	x	x

The occurrence of any clinical event included in the end-points will be notified. An independent ad hoc committee of expert clinicians, identified by the Steering Committee, will validate all the clinical events.

Moreover, information on any adverse event, including side effects of study treatments, will be collected.

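### The lead efficacy test is an unadjusted logrank although strong prognostic baseline values are already collected; making a pre-specified adjusted Cox model primary would add modest power at almost no cost

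*Protocol article*

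**What the plan says.** The Statistical analysis section of the protocol article makes two comparisons of the arms on efficacy. The first is "Incidence rates (aspirin vs. no aspirin) will be estimated using Kaplan-Meier survival curves that will be compared using logrank analysis". The second is introduced as an extra: "Additionally, treatment efficacy will be assessed by multivariate analyses using Cox's regression model". Neither is labelled primary, no strata or covariates are named for the logrank, and no covariates are listed for the Cox model.

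Sample size estimates refers to one analysis: "a total of 515 first events are needed for the primary efficacy analysis".

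Under Data collection, the entry data cover "clinical data regarding diabetes, cardiovascular risk factors, and selected concomitant medications", together with laboratory values. Table 1 lists blood pressure, HbA1c, creatinine, albumin/creatinine ratio and lipids at month 0. The planned subgroups use sex, age, diabetes type, HbA1c, and total and LDL-cholesterol, so these must be known at baseline as well.

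On allocation, Study treatments says: "A separate computer-generated randomization table will be produced for each physician/diabetes centre in random permuted blocks".

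**The concern.** The population is people aged 50 and over with type 1 or type 2 diabetes, whose baseline cardiovascular risk is likely to vary widely. When risk varies and the test ignores it, the hazard ratio estimated without covariates lies closer to 1 than the hazard ratio between patients of the same risk. A test that uses the main risk factors then has somewhat more power at the same number of events.

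The data needed are already in the plan, so the only question is which of two planned analyses should lead. A small gain is worth having here. The trial is event-driven, with follow-up prolonged until 515 events are reached. The Background also reports reductions of only 7% and 10%, neither significant, in earlier patients with diabetes, so the true effect may be smaller than the 25% assumed.

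**Working it through.** **1. Which test the plan is built on.** Inputs from Sample size estimates: hazard ratio 0.75, power 90%, α = 0.05 (sidedness not stated), 1:1 allocation. With two-sided α, (1.960 + 1.282)² = 10.507.

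- Freedman logrank formula: events = ((1 + HR)/(1 − HR))² × 10.507 = (1.75/0.25)² × 10.507 = 49 × 10.507 = 514.9, that is 515. This matches the plan exactly.
- Schoenfeld formula: 4 × 10.507/(ln 0.75)² = 508, within 2% of the plan.
- One-sided versions give 420 and 414 and do not fit.
- The second power statement also reproduces. At HR 0.78 and 515 events, √515 × 0.22/1.78 − 1.960 = 0.845, which is power 80.1% (stated: 80%).

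The order of the two sentences and the sample size therefore agree: the lead test is the unadjusted logrank.

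**2. Power of that test.** Schoenfeld form: power = Φ(√515/2 × |ln HR| − 1.960). At HR 0.75: Φ(11.347 × 0.2877 − 1.960) = Φ(1.304) = 90.4%.

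**3. Power with adjustment.** The protocol gives no figure for how strongly baseline factors predict events. Assumption: a normal risk score on the log-hazard scale, with SD between 0.5 and 1.0. A very large simulated population was used, with 18 months of accrual, a 5-year study and about 9–10% of patients with an event (515/5,170 = 10.0%). It gave the factor by which ignoring the score shrinks the log hazard ratio. The unadjusted HR is held at 0.75, so the conditional HR is exp(ln 0.75/factor). Power and Freedman events then follow from the formulas above.

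| Assumed SD | AUC of score | Shrinkage factor | Conditional HR | Power, adjusted | Events for 90% |
|---|---|---|---|---|---|
| none | – | 1 | 0.750 | 90.4% | 515 |
| 0.5 | 0.65 | 0.988 | 0.7474 | 91.1% | 503 |
| 0.7 | 0.70 | 0.970 | 0.7434 | 92.0% | 485 |
| 0.8 | 0.72 | 0.955 | 0.7398 | 92.8% | 470 |
| 1.0 | 0.77 | 0.940 | 0.7363 | 93.5% | 456 |

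Example, SD 1.0: Φ(11.347 × 0.3061 − 1.960) = Φ(1.514) = 93.5%. Events fall by 515 − 503 = 12 (2%) to 515 − 456 = 59 (11%).

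The simulation error of the shrinkage factor is about 0.6%. In a run with no prognostic score it shifted power by 0.4 points, so the 0.7-point gain at SD 0.5 is barely above the noise.

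**4. Where the gain comes from.** In simulated trials of the planned size (SD 0.8, about 480 events), the standard error of the log hazard ratio was 0.092 both with and without adjustment. Only the estimate moved, away from 1.

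**5. Stratifying by centre.** The number of centres is not given. With 100, 250 or 400 assumed centres, blocks of 4 and a between-centre SD of 0 or 0.3, a centre-stratified logrank carried about 0.98 to 1.00 times the information of the unstratified one. Small strata with few events contribute no gain.

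**The case against.** The strongest reply is that nothing here is wrong. The logrank is valid under intention to treat, it matches the event calculation, and a multivariate Cox analysis is already planned in the next sentence. The gain is 1 to 3 power points, rests on assumed SDs, and treats the risk score as known without error. Adjustment also changes the estimand, and a covariate list may sit in an analysis plan that is not shown. All of this stands, and it limits the point to an efficiency improvement. It does not remove the point, because the order of the two analyses is a stated choice and not a detail left out.

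A reader might infer more, and the documents do not support it:

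- *That baseline factors are ignored.* They are not, since the additional Cox model is planned.
- *That the test should follow the randomization tables by physician or centre.* The article is silent on strata, which a condensed article may leave to a fuller document, and step 5 shows that such strata would recover nothing.
- *That precision is lost.* The standard error is the same either way.
- *That the planned test falls short of 90% power.* If 0.75 were the conditional hazard ratio, unadjusted power at 515 events would be 89.7% to 86.6% for SD 0.5 to 1.0. But the protocol takes its 25% from published aspirin effects and pairs it with a logrank event count, which fits reading 0.75 as the unadjusted value. On that reading the stated power is met.

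**Conclusion.** The point holds as an optional but nearly free improvement. The unadjusted logrank is sound and delivers its stated 90% power at HR 0.75 with 515 events. Putting an adjusted Cox model first would raise power by about 1 to 3 points, to 91.1–93.5%, equivalent to needing about 2–11% fewer events. This depends on an unadjusted HR of 0.75 and on an assumed log-hazard SD of 0.5 to 1.0 captured by the chosen covariates. At the low end of that range the gain is close to negligible.

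**What to change.** In the Statistical analysis section, name one primary test: a Cox model for aspirin against no aspirin, adjusted for a few covariates fixed in advance. Examples are age, sex, diabetes type, HbA1c, LDL-cholesterol, systolic pressure, creatinine and statin use at entry. Keep the unadjusted logrank and the Kaplan-Meier curves as supportive. Do not stratify the test by individual physician or centre. The 515-event target can stay as it is. Naming the primary test also settles which statistic the 3-standard-deviation interim criterion refers to.

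The cost is wording plus two small duties:

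- The adjusted hazard ratio must be described as conditional on the listed covariates, and not as the same quantity as the unadjusted one.
- A rule for missing baseline values must be set beforehand. Few should be missing, because Data collection already asks for old laboratory values to be measured again around randomization. Table 1 lists total and HDL cholesterol and triglycerides but not LDL, so the rule should say how baseline LDL is obtained.

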#### Primary objectives

To assess the effects of low dose aspirin on the incidence of major vascular events (defined as a combined end-point of cardiovascular death, non-fatal myocardial infarction, non-fatal stroke, or inpatient or outpatient hospital admission for cardiovascular causes, including acute coronary syndrome, not planned revascularization procedures, peripheral vascular disease), in a wide range of people with type 1 or type 2 diabetes with no clinical evidence of vascular disease and receiving statins treatment.

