#### Secondary objectives

Additional aspects to be considered will include total and cause specific mortality, venous thromboembolic episodes, major hemorrhagic episodes, and total number of hospitalizations for cardiovascular causes (myocardial infarction, stroke, acute coronary syndrome, not planned revascularization procedures, heart failure, transient ischemic attack, peripheral vascular disease, lower limb revascularization procedures).

The study will also describe the natural history of the disease under routine clinical practice conditions, particularly with reference to the degree of control of the other cardiovascular risk factors.

The coherence in the effects of low dose aspirin across different patients subgroups defined according to their baseline characteristics/risk (i.e. gender, age, type of diabetes, metabolic control, baseline cholesterol levels, presence of microvascular complications, treatment with other cardiovascular drugs) will also be assessed.

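### One minus Kaplan-Meier slightly overstates the incidence of the primary composite in each arm, because non-cardiovascular death lies outside the end-point

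*Protocol article*

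**What the plan says.** The Statistical analysis section names one estimator of incidence and one test: "Incidence rates (aspirin vs. no aspirin) will be estimated using Kaplan-Meier survival curves", and the curves are to be compared by the log-rank test. It adds that "treatment efficacy will be assessed by multivariate analyses using Cox's regression model". No other estimator of incidence is named.

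The Primary objectives section limits the fatal part of the primary end-point to cardiovascular causes. The composite is "defined as a combined end-point of cardiovascular death, non-fatal myocardial infarction, non-fatal stroke, or inpatient or outpatient hospital admission for cardiovascular causes". Death from any other cause is not a primary event, but it ends the possibility of one.

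The Secondary objectives section lists "total and cause specific mortality", so cause of death will be recorded. The article does not say how non-cardiovascular deaths enter the Kaplan-Meier curves, gives no expected rate for them, and does not mention competing risks.

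**The concern.** Patients are at least 50 years old, have diabetes, and are to be followed for several years. Some will die of non-cardiovascular causes before any primary event. A standard Kaplan-Meier curve for the composite treats such a patient as censored, that is, as someone who could still have an event later. One minus the curve then describes a hypothetical population in which nobody dies of other causes. It is higher than the proportion of patients who actually have a primary event. This direction holds in each arm as soon as any such death occurs, whatever the rate.

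What is at stake is the description of absolute risk. The arm-specific incidences are what a reader would subtract to judge the benefit of aspirin in primary prevention. The Interim analyses section also frames early stopping partly in terms of a net difference in how often the major end-point occurs.

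**Working it through.** **Inputs from the Sample size estimates section**
- Event rate without aspirin: λ₀ = 0.025 per year ("conservative estimated 2.5% annual rate of major vascular events", taken here as the no-aspirin rate).
- Effect: HR 0.75, so with aspirin λ₁ = 0.75 × 0.025 = 0.01875 per year.
- Follow-up: T = 5 years.
- 515 events, 90% power, α = 0.05; 2,585 patients per arm.

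**Assumptions**
- Non-cardiovascular death rate m: no figure in the article; 0.005 to 0.03 per year is used.
- Constant hazards.

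**Step 1: the plan's own figure.** Freedman's formula with a two-sided α gives ((1 + 0.75)/(1 − 0.75))² × (1.960 + 1.282)² = 49 × 10.507 = 514.9, so 515. The event count is reproduced. It depends on the hazard ratio, α and power only, so m does not enter it.

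**Step 2: what Kaplan-Meier targets.** With other-cause deaths censored, it is 1 − exp(−λT).
- Without aspirin: 1 − exp(−0.125) = 11.75%.
- With aspirin: 1 − exp(−0.09375) = 8.95%.
- Difference: 2.80 points.

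**Step 3: cumulative incidence with other-cause death as a competing event.** It is λ/(λ + m) × [1 − exp(−(λ + m)T)]. For m = 0.01:
- Without aspirin: (0.025/0.035) × [1 − exp(−0.175)] = 0.7143 × 0.1605 = 11.47%.
- With aspirin: (0.01875/0.02875) × [1 − exp(−0.14375)] = 0.6522 × 0.1339 = 8.73%.

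With the same m in both arms:

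| m per year | No aspirin | Aspirin | Difference (points) | Relative excess of Kaplan-Meier, no aspirin / aspirin |
|---|---|---|---|---|
| Kaplan-Meier | 11.75% | 8.95% | 2.80 | – |
| 0.5% | 11.61% | 8.84% | 2.77 | 1.2% / 1.2% |
| 1% | 11.47% | 8.73% | 2.74 | 2.5% / 2.5% |
| 2% | 11.19% | 8.52% | 2.67 | 5.0% / 5.0% |
| 3% | 10.93% | 8.32% | 2.61 | 7.5% / 7.6% |

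The absolute difference is overstated by 0.03 to 0.19 points. The reciprocal of the difference is 35.7 by Kaplan-Meier, against 36.6 at 1% and 37.4 at 2% per year.

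**Step 4: unequal other-cause death by arm.** With m = 1.0% without aspirin and 1.5% with aspirin, the cumulative incidences are 11.47% and 8.63%. The difference is 2.84 points, above the Kaplan-Meier 2.80. With 1.0% and 0.5%, they are 11.47% and 8.84%, a difference of 2.63 points. The error in the difference has no fixed sign.

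**Step 5: length of follow-up.** The Timing section counts five years from the first randomized patient with 18 months of enrolment, so the last patient would have about 5 − 1.5 = 3.5 years. Putting T = 3.5 and m = 1% into the same formulas for the no-aspirin arm gives 8.38% against 8.24%, a relative excess of 1.7%. If follow-up is prolonged, as the Timing section allows, the gap grows: at an illustrative T = 8 it is 18.13% against 17.44% (3.9%) at m = 1%, and 18.13% against 16.80% (7.9%) at m = 2%.

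**Step 6: scale against sampling error.** With 2,585 per arm, the standard error of the difference is about √[(0.1175 × 0.8825 + 0.0895 × 0.9105)/2585] = 0.0085, or 0.85 points. At m = 1% to 2% the overstatement of the difference, 0.07 to 0.13 points, is less than a sixth of one standard error.

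**The case against.** The strongest reply is that the article never says non-cardiovascular deaths are censored, and that censoring and competing-risk rules usually stand in the full protocol or the analysis plan, which are not shown. The first half is correct, and the point here rests on inference. The second half does not dispose of it. The article itself names the estimator of incidence, and in its ordinary form that estimator cannot handle these deaths other than by censoring. This is a stated choice with a better alternative, not a missing detail.

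A second reply is that the effect is negligible beside sampling error and rests on a death rate the article does not give. The size is indeed small. But the excess is systematic, has a known direction within each arm, and grows with follow-up.

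Three stronger readings are tempting, and the document does not support them.
- A reader might infer that the plan inflates the benefit of aspirin. That needs both a true effect and similar non-cardiovascular death in the two arms; Step 4 shows the opposite result when the rates differ.
- A reader might infer that a planned absolute risk reduction or number needed to treat is biased. Neither is named as an estimate. The planned effect is a hazard ratio, although two incidence curves invite the subtraction.
- A reader might infer that the same error is built into cause-specific mortality, venous thromboembolism and major haemorrhage. The section names no incidence estimator for the secondary end-points, so this can only be said if Kaplan-Meier were used for them too. In that case a low-rate bleeding end-point would be inflated by a similar proportion, so the balance of benefit and bleeding would hardly move.

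**Conclusion.** The point holds as a minor one. Kaplan-Meier is named as the estimator of incidence for an end-point that excludes non-cardiovascular death. If applied in the ordinary way, it overstates the incidence of the primary composite in each arm. The direction needs no assumption beyond the occurrence of such deaths. The size, roughly one to eight per cent in relative terms at five years, rests on constant hazards and on the assumed range of non-cardiovascular death. The effect on an absolute difference is small and its sign is conditional.

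The log-rank test and the Cox hazard ratio remain valid as cause-specific comparisons, and the 515-event target does not change. The conclusion on whether aspirin works is therefore not threatened; only the description of absolute risk is.

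**What to change.** State in the analysis plan that incidence of the primary composite is estimated and plotted by arm with Aalen-Johansen cumulative incidence functions, with non-cardiovascular death as the competing event. Keep the log-rank test and the Cox model, and label them as cause-specific comparisons. Wherever incidence of a cause-specific or non-fatal secondary end-point is reported, use the same estimator, with death from causes outside that end-point as the competing event. Take any absolute difference between arms from these functions, and show non-cardiovascular death by arm beside it, so that a reader can see whether it differs.

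The cost is a few lines of text and slightly more analysis work with standard software. No extra data are needed, because cause of death is already required for a secondary end-point. Sample size, event target and the primary test stay as they are.
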